## Trial procedures

### Recruitment

Potential study participants will be identified by the critical care outreach team, who are required to review every patient placed on NIV either on the wards or in the emergency department. The outreach team will inform the research team of potential study participants. The research team is available 24 h, 7 days.

### Informed consent

Informed consent/assent will be taken by appropriately trained investigators. Informed consent will be obtained prior to any study-related procedures being undertaken. The study participant or, if they lack capacity at the time of enrolment, the patient’s consultee must personally sign and date the latest approved version of the informed consent form before any study-specific procedures are performed.

Written and verbal versions of the participant information and informed consent will be presented to the participants detailing no less than: the exact nature of the study; the implications and constraints of the protocol; the known side effects and any risks involved in taking part. It will be clearly stated that the participant is free to withdraw from the study at any time for any reason without prejudice to future care, and with no obligation to give the reason for withdrawal.

The participant or their consultee will be allowed up to 2 h to consider the information, and the opportunity to question the investigator or other independent parties to decide whether they will participate in the study. Written informed consent will then be obtained by means of participant or their consultee dated signature and dated signature of the person who presented and obtained the informed consent. The person who obtained the consent must be suitably qualified and experienced and have been authorised to do so by the Chief/Principal Investigator. A copy of the signed informed consent will be given to the participants or their consultee. The original signed form will be retained at the study site. Once any participant has regained capacity they will be given written and verbal information about the study. Written informed consent will then be obtained by means of participant dated signature and dated signature of the person who presented and obtained the informed consent. It will be clearly stated that the participant is free to withdraw from the study at any time for any reason without prejudice to future care, and with no obligation to give the reason for withdrawal (Additional files 1).

### Randomisation and codebreaking

Randomisation will be achieved using a computer-generated random list then stored as sequential sealed envelopes accessible to the primary study team. Other sites will randomise by telephone to the lead centre with envelopes opened and accessible only to the primary study team. The study participants, care providers and outcome assessors will be unblinded (open label).

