## Trial hypothesis and objectives

The main hypotheses for the trial are that ECCO_2_R will lead to a significant reduction in the need for NIV and that this is mediated through a reduction in work of breathing secondary to the reduced CO_2_ burden. To explore work of breathing, several methods of assessing work of breathing will be undertaken: oesopheageal pressure monitoring, electrical impedance tomography and parasternal electromyography. These methods have not been used in combination before in this population; however, the benefit of using multimodal monitoring in the setting of acute exacerbations of COPD is that it will allow correlation between the different measurements and it is possible that one or more methods may not be able to be used in an individual patient.

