EIT will be undertaken unless there is a contraindication (pacemaker or implantable defibrillator). EIT examinations will be performed using the Drager Pulmovista 500 EIT device (Pulmovista®; Draeger, Luebek, Germany) using a silicone band consisting of 16 integrated electrodes and one reference electrode applied around the thorax at the fourth intercostal space in accordance with the manufacturer’s instructions. Real-time analogue waveform outputs from the ventilators feed to an inbuilt data acquisition system (Draeger EIT Data Analysis Tool 6.1). Data will be analysed after processing using custom-made software and in accordance with the method described by the Translational EIT Development (TREND) study group [51]. Data will be displayed to demonstrate changes in tidal volume, end-expiratory lung volume, spatial distribution of gas and respiratory time constants [67–70]. Descriptors of the spatial distribution of ventilation, including the global inhomogeneity index [71–74] and the coefficient of variation [61, 72, 75], will be reported. Additionally, the heterogeneity of ventilation will be quantified measuring regional respiratory time constants [69, 70], phase shifts in regional ventilation [76], the ventilation delay index [77] and heterogeneity of expiratory times [61, 62, 78].

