#### Parasternal electromyography

Exacerbations of COPD result in an increase in the subjective work of breathing, anxiety and tachypnoea, which in turn result in a progressive increase in the elevated neural respiratory drive mediated through the respiratory centre in the brainstem [79–81]. Although the output of the respiratory centre cannot be measured directly, a well validated surrogate measure is the electromyography (EMG) signal measured at the level of the parasternal intercostal muscles using surface electrodes placed over the second intercostal space [80, 82–84]. Parasternal EMG has been demonstrated to be a reproducible and well tolerated technique to assess neural respiratory drive [85], particularly for patients with an exacerbation of COPD [80, 81]. To allow physiologically meaningful comparisons of the EMG signal, the root mean square is used to quantify the intensity and duration of the contraction and has been shown to be linearly associated with increasing load on the muscle [86, 87]. Additional measures to quantify the neural respiratory drive are the percentage of the EMG signal of the maximum EMG signal obtained (EMG_para%max_) and the neural respiratory drive index (NRDI), which is the product of EMG_para%max_ and the respiratory rate [80]. NRDI is a validated measure of work of breathing during an acute exacerbation and allows changes in work of breathing over time to be documented [80, 81].

EMG will be recorded from the parasternal second intercostal space bilaterally and then processed and analysed in accordance with previously published work [80, 81]. The root mean square will be used to calculate the root mean square EMG_para%max_ from the maximum EMG signal obtained and the NRDI will be calculated by multiplying EMG_para%max_ by the respiratory rate. Changes in an individual patient will then be analysed over time.

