Oesophageal pressure measurements will be undertaken using a 5 French latex free balloon catheter (Cooper Surgical, Conneticut, USA) inserted into the lower oesophagus trans-nasally with 0.5–1.5 mL of air instilled to allow optimal transmission of the pressure waveform [91]. The catheter is attached to a pressure transducer to obtain pressure measurements and simultaneous pneumotachograph recordings are made (Hans Rudolph differential pneumotachograph). The balloon position will be validated using the dynamic occlusion test in the spontaneously breathing patient [92, 93].). All signals will be collected on a personal computer through a 12-bit analogue-to-digital converter (National Instrument DAQCard 700; Austin, TX) at a sampling frequency of 200 Hz (ICU-lab, KleisTEK Engineering, Bari, Italy). Signals will be analysed using ICU-Lab software. The oesophageal pressure trace will be used to calculate work of breathing and the pressure time product will be calculated. Oesophageal pressure will be used solely as an outcome measure and will not be available for use at the bedside.

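### The blanket statement that outcome assessors are unblinded also covers work-of-breathing signals analysed offline, which leaves an avoidable risk of detection bias in the mechanism results

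*Protocol article*

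**What the plan says.** On blinding, the section on randomisation and codebreaking has one sentence: "The study participants, care providers and outcome assessors will be unblinded (open label". It makes no exception for any outcome.

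The sections on the three work-of-breathing measures describe analysis after recording:

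- **EIT:** "Data will be analysed after processing using custom-made software and in accordance with the method described by the Translational EIT Development (TREND) study group".
- **Parasternal EMG:** "EMG will be recorded from the parasternal second intercostal space bilaterally and then processed and analysed in accordance with previously published work". The derived indices are scaled to the largest EMG signal obtained, and one of them is then multiplied by respiratory rate.
- **Oesophageal pressure:** the signals are collected on a computer, and "Signals will be analysed using ICU-Lab software". The same section adds: "Oesophageal pressure will be used solely as an outcome measure and will not be available for use at the bedside".

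The trial hypothesis is that ECCO2R reduces the need for NIV and that "this is mediated through a reduction in work of breathing". The abstract plans physiological comparisons both within a patient over time and between the two groups. Work of breathing is listed among the secondary outcomes.

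**The concern.** In this trial there are two different reasons for an assessor to be unblinded. At the bedside it cannot be avoided, since the circuit is visible. For a stored signal it is a choice, because the file can be coded and analysed by someone who does not know the arm. The article treats both cases alike.

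What is at stake is the mechanism half of the main hypothesis. If deriving a value leaves the analyst any discretion, knowing the arm or the study day could move results in the expected direction. That applies to the contrast between arms and also to the change within a patient, where the analyst would know which recording came earlier. The statistical analysis section puts the physiological data on a per-protocol basis, so these comparisons already lack the full protection of randomisation. Masked derivation is one of the few safeguards still available to them.

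**Working it through.** **1. Is the arm masked from the analyst anywhere in the article?** Four provisions might seem to do so.

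| Section | Provision | What it hides |
|---|---|---|
| Data collection | De-identified storage, sequential trial number | The patient's identity, not the arm |
| Oesophageal pressure monitoring | Trace withheld from bedside use | The signal from clinicians, not the arm from the analyst |
| Electrical impedance tomography | Custom software, published method | Nothing; it standardises the calculation |
| Parasternal electromyography | Published processing method | Nothing; it standardises the calculation |

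None masks the arm, and the only sentence on assessor blinding says that assessors are unblinded.

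**2. The plan's own figure.** The sample size section gives 12 per arm, a difference of 12 h, an SD of 10 h, alpha 5% (two-sided assumed) and 80% power. For a two-sample t-test:

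- standardised difference d = 12/10 = 1.2
- noncentrality = d × √(n/2) = 1.2 × √6 = 2.94, with 2n − 2 = 22 degrees of freedom
- power = 0.802

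The stated 80% reproduces. It concerns NIV duration, and masking the signal analysts would not change it.

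**3. Illustration of what a reading shift could do.** The article gives no size for such a shift, so every value here is an assumption. Take a work-of-breathing measure with no true difference between arms, 12 per arm, and a systematic shift of b SD between arms introduced in derivation. The false-positive rate is then the power of the test at d = b. For b = 0.5, the noncentrality is 0.5 × √6 = 1.22.

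| Assumed shift b (SD) | Two-sided 5% t-test (noncentral t) |
|---|---|
| 0 | 5.0% |
| 0.10 | 5.6% |
| 0.25 | 9.0% |
| 0.50 | 21.6% |
| 0.75 | 42.0% |

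The article names the Mann-Whitney test for the primary outcome and similar analyses for secondary efficacy data. With the exact Mann-Whitney test (20,000 simulated normal trials), the rates are 4.2% at no shift, 9.7% at 0.3 SD, 19.9% at 0.5 SD and 42.9% at 0.8 SD. Both tests therefore give about 20% at 0.5 SD.

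**4. Limits of the illustration.** It assumes that all 12 patients per arm contribute a value. Fewer would be available after EIT contraindications or per-protocol exclusions, and the same shift in SD units would then inflate the rate less. It models only the contrast between arms, not the within-patient comparison. The same rates would follow in any trial of this size, so they are not evidence about this one.

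**The case against.** The strongest reply is that the blinding sentence names three roles and says nothing about whoever processes stored recordings, and that the sections on the three signals do not say who that is. Masking of signal analysts could then be a detail left to the full protocol or the analysis plan. It is true that the sentence does not name these signals. But work of breathing is a listed outcome, deriving its value is assessing it, and the sentence is an unqualified statement rather than a silence. If masking is in fact planned, the sentence is too broad and needs narrowing.

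A second reply is that the indices come from software and published methods, which may leave little to a reader's judgement. This stands as a limit on the point. A reader might infer that the analyst chooses which breaths to keep, which stretches to reject as artefact and which peak counts as the maximum EMG. Those are plausible steps, but the article does not describe them, so the amount of discretion is unknown. For the same reason one cannot conclude that the results are biased.

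A third reply is that masking would be incomplete, and this also stands. Daily recordings continue while a patient is on either NIV or ECCO2R, so an ECCO2R patient may be recorded off NIV. Ventilator waveforms feed the EIT acquisition system. The presence or absence of NIV in a trace may therefore point to the arm whatever the file code, and the person who made a recording may remember it.

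Finally, it would be too much to say that the article calls physiology its most informative part. The discussion says only that no definitive answer on mortality or intubation is expected and that the physiology should improve understanding.

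**Conclusion.** The point holds as an avoidable risk of detection bias in secondary, mechanistic outcomes. The article declares assessors unblinded without exception, the three signals are analysed after recording, and nothing shown masks the arm from the analyst. No bias is demonstrated, and the article offers no basis for estimating one. The figure of about 20% rests entirely on an assumed 0.5 SD shift between arms with no true effect and 12 patients contributing per arm; at 0.1 SD the rate would be 5.6%. The primary outcome, the sample size and the stated power are unaffected. This is a cheap improvement, not a flaw that undermines the trial.

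**What to change.** Limit the unblinded statement to participants, care providers and bedside assessments. For EIT, EMG and oesophageal pressure:

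- export the stored recordings under random file codes, with the arm removed and the study day removed where possible;
- set segment-selection and artefact rules, and the rule for the reference maximum EMG, before processing;
- have existing staff derive the values in batches, preferably someone who did not make the recording;
- lock the derived values, then merge allocation and day.

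If masking is judged impossible for a signal, say so and give the reason. Recordings already processed could be reprocessed from stored files, since the trial has only 24 patients.

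The cost is some file handling and a delay while batches accumulate. Recording, visits and patient care do not change. Because masking will be partial, the report should state how far it was achieved.

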### Data collection

For eligible patients, clinical details will be collected after consent has been obtained and randomisation undertaken (Fig. 1). This will include details to confirm eligibility and basic demographic and medical details, including acute and chronic co-morbidity and medicines as well as a full physical examination. Details of baseline routine clinical investigations will be recorded. Participants will be allocated a sequential trial number to ensure participant anonymity and confidentiality. All data will be stored in de-identified password-protected databases held within the NHS. All paper documents will be transferred to the department of Critical Care at Guy’s and St Thomas’ NHS Foundation trust and stored in locked, fire-proof cabinets. All data transfers between institutions will conform to the information governance requirement of the NHS.

**Fig. 1 Fig1:**
[figure not shown]
Example template of recommended content for the schedule of enrolment, interventions, and assessments (recommended content can be displayed using various schematic formats; see SPIRIT 2013 Explanation and Elaboration for examples from protocols) (Additional File 2). **List specific timepoints in this row

### Treatment of trial participants

Following presentation, initial medical therapy and NIV will be commenced as per current local and UK national guidelines for the management of AECOPD [47]. All patients with AECOPD and pH < 7.30 after a minimum of 1 h NIV will be eligible for inclusion unless exclusion criteria are met. Once informed written consent is obtained from either the patient or their consultee if consent from the patient is not possible, patients will be randomised to the continuation of NIV alone or addition of ECCO_2_R to NIV. All other aspects of care, including acute, on-going and post-trial care, will be at the discretion of the clinical team. Monitoring will be the standard of care of ICU, including arterial and central venous access where this is deemed appropriate by the clinical team.

Patients who are randomised to continuation of NIV alone will be managed in accordance with hospital protocols and national guidelines for NIV. NIV will be titrated to achieve an arterial pH > 7.35, respiratory rate < 25 and patient comfort with breathing. Discontinuation of NIV will occur when judged appropriate by the patient’s clinician. Cessation of NIV will be defined as occurring after six continuous hours without NIV.

#### ECCO_2_R

Patients who are randomised to addition of ECCO_2_R will undergo cannulation in either the right internal jugular vein or one of the femoral veins using a 15.5 French double lumen ECCO_2_R cannula (patient and operator preference) using an ultrasound-guided Seldinger technique. The ECCO_2_R device, will be primed with 0.9% saline and 1 unit/mL heparin in accordance with the manufacturer’s instructions. The blood flow will be titrated to the maximum achievable (usually 400–500 mL/minute) and sweep gas titrated up to 10 L/minute in 1 L/minute increments every 15 min. ECCO_2_R will be titrated to achieve an arterial pH > 7.35, respiratory rate < 25 and patient comfort with breathing. Discontinuation of NIV and ECCO_2_R will occur when judged appropriate by the patient’s clinician. Cessation of ECCO_2_R will be defined as occurring after six continuous hours without ECCO_2_R. All patients receiving ECCO2R will receive a continuous infusion of heparin to maintain an APTTr of 1.5–2 titrated using the hospital protocol. Data relating to the ICU inpatient stay will be collected from the ICU and hospital information systems. At 3 months following randomisation, a telephone interview will be conducted by the randomising study centre to ascertain the post-discharge survey data.

Whilst the patient remains on respiratory support (either NIV or ECCO_2_R), all patients will undergo daily assessment of dyspnoea and comfort, spirometry, electrical impedance tomography, parasternal electromyography and oesophageal pressure monitoring.

#### Electrical impedance tomography

Electrical impedance tomography (EIT) is a non-invasive, bedside monitoring technique that provides semi-continuous, real-time information about the regional distribution of the changes in electrical resistivity of the lung tissue due to variations in ventilation (or blood perfusion) in relation to a reference state [48–50]. To generate an image, EIT repeatedly injects small alternating electric currents (usually 5 mA) at high frequency of 50–80 kHz through a system of 16 skin electrodes applied circumferentially around the thorax in a single plane between the fourth and sixth intercostal space [51, 52]. While an adjacent pair of electrodes ‘injects’ the current, the remaining passive electrode pairs measure the differences in electric potential. A resistivity (impedance) image is reconstructed from these data by a mathematical algorithm [48–50]. Lungs have a changing impedance during the respiratory cycle due to changes in the air–tissue ratio. This variation in tidal impedance provides quantitative data on both changes in lung volume and regional distribution of air within the lung, allowing the recording of physiological phenomena with high temporal and functional resolution [53–56].

COPD is known to have significant spatial and temporal heterogeneity of ventilation due to the inhomogenous destruction of lung elastic tissue leading to loss of elastic recoil, regional ventilation inequality, increased airway resistance and dynamic hyperinflation. One of the key problems in exacerbations of COPD is the prolongation of the expiratory phase in COPD, resulting in the development of dynamic hyperinflation which leads to haemodynamic compromise, increased work of breathing and ventilator asynchrony [57, 58]. Information derived from EIT indices, including the global inhomogeneity index, can be used to demonstrate both inhomogeneous ventilation and the development of dynamic hyperinflation [59–64]. One potential method to demonstrate dynamic hyperinflation is the mapping of expiratory time constants using the change in impedance over time [65, 66]. It is anticipated that time constants will correlate with other measures of global inhomogeneity and this will be used to describe the physiological consequences of NIV and ECCO_2_R.

EIT will be undertaken unless there is a contraindication (pacemaker or implantable defibrillator). EIT examinations will be performed using the Drager Pulmovista 500 EIT device (Pulmovista®; Draeger, Luebek, Germany) using a silicone band consisting of 16 integrated electrodes and one reference electrode applied around the thorax at the fourth intercostal space in accordance with the manufacturer’s instructions. Real-time analogue waveform outputs from the ventilators feed to an inbuilt data acquisition system (Draeger EIT Data Analysis Tool 6.1). Data will be analysed after processing using custom-made software and in accordance with the method described by the Translational EIT Development (TREND) study group [51]. Data will be displayed to demonstrate changes in tidal volume, end-expiratory lung volume, spatial distribution of gas and respiratory time constants [67–70]. Descriptors of the spatial distribution of ventilation, including the global inhomogeneity index [71–74] and the coefficient of variation [61, 72, 75], will be reported. Additionally, the heterogeneity of ventilation will be quantified measuring regional respiratory time constants [69, 70], phase shifts in regional ventilation [76], the ventilation delay index [77] and heterogeneity of expiratory times [61, 62, 78].

